#### Dropout criteria of the secondary target group

Nursing staff may withdraw their consent to participate at any time. They can do this by revoking their consent to participate in writing.

In addition, nursing staff can be excluded from the study if their poor technical affinity or acceptance leads to massive restrictions concerning the correct implementation and use of the digital assistance system in the context of incontinence care. In order to ensure a correct application of the technology, training sessions for the nursing staff will be held over several days at the beginning of the measurement period. During this training nursing staff will be introduced in depth to the digital assistance system. This is followed by a test phase of one to two weeks in the inpatient care facility, during which the nursing staff independently tests the system in regular care. If, during this period, a professional is found to lack technical user skills or feedback is received from the person concerned, this person will not continue to participate in the study.

For both the primary and secondary target groups, further progression of the Covid pandemic may result in exclusion or withdrawal from the study. If, in an inpatient care facility, a Covid outbreak is deemed by management to have a lasting impact on normal business operations, the facility may decide to not continue its participation in the measurements.

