**Aims and methods:**

This RCT aims to validate the benefits of using a digital assistance system to optimise incontinence care and to enable statements concerning the effect of the assistance technology on nursing and social structures and processes as well as on the quality of life from the perspective of the person in need of care. In a two-arm, stratified, randomised, controlled interventional study, primarily incontinence-affected residents of four inpatient nursing facilities will be examined (*n* = 80). One intervention group will be equipped with a sensor-based digital assistance system, which will transmit care-related information to the nursing staff (via smartphone). The collected data will be compared to the data of the control group. Primary endpoints are falls occurring; secondary endpoints are quality of life and sleep, sleep disturbances and material consumption. In addition, nursing staff (*n* = 15–20) will be interviewed regarding the effects, experience, acceptance and satisfaction.

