#### Endpoints of the secondary target group (nursing staff)

The secondary target group will be surveyed by means of interviews regarding the acceptance, experience and perceived effects of the digital assistance systems and the resulting changes to their work processes (secondary endpoints). This qualitative data collection captures the important perspectives of nursing staff and nursing management.

In addition, the nursing staff will also be surveyed quantitatively about their subjective attitude toward the use of technology in their professional context and concnerning the use of the digital assistance system in particular. The subscales of the questionnaire to measure the affinity for technology scale (TA-EG) are used as guidance. The TA-EG consists of 19 items and four scales and has been adequately reviewed in terms of its validity and reliability. Due to its scope, it will be used in a shortened form in the study and adapted to the specific core of the intervention. The modified questionnaire was tested in pretests with regard to comprehensibility, practicability and temporal scope. Subsequently, editorial changes were incorporated (see Table 1).

**Table 1 Tab1:** Endpoints and measurement tools for the primary target group

Primary endpoints	Measurement tools
Incipient falls	**STRATIFY instrument** (St. Thomas’s risk assessment tool in falling elderly inpatients) [39] • Includes five items / risk factors • Confirmed validity and reliability [40] • Quantitative method, third-party assessment **Tinetti Test** [41] • Includes 17 items • Confirmed validity and reliability [42] • Quantitative method, third-party assessment **Extrinsic and intrinsic risk factors** for the residents • based on and correlating with the national expert standard on incontinence of the German Network for quality standards in care-giving (DNQP) [11] **Analysis of fall records** • Documentation through the nursing facility is mandatory • Provides important information about occurring falls and possible consequences of falls
**Secondary endpoints**	**Measurement tools**
Cognitive ability	**Mini Mental Status Examination (MMSE)** [36] • Consists of five categories with a total of 11 items • Confirmed validity and reliability • Used for stratification • Quantitative method, self-reported scale

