### Power calculation

The sample size calculation is based on the RCT by Chittrakul et al. [51] in which a special exercise program for fall prevention to avoid falls and increase the quality of life was developed. The result of the RCT was that the participants in the IG fell on average 1.13 times (SD = 0.84) and in the CG the average was 2.22 [51]. For the current sample size calculation, a more conservative estimate was made (M = 1.65) since a less intensive intervention is to be studied that is nevertheless of high clinical relevance. To detect a significant difference between the two groups in a two-arm test with a significance level of 0.05 and 80% power, we need at least 34 persons in each group. Thus, a total of at least 68 persons will be included. Due to the high vulnerability of the sample and assuming a drop-out rate of about 15%, a total of 80 indiviudals will be included with 20 participants from each nursing facility (primary target group). The participants will be divided into an intervention group and a control group.

Concerning the nursing staff, as secondary target group, about six to eight individuals in each inpatient facility, who are responsible for the incontinence care of the participants in the primary target group and routinely use the assistance system in their daily professional practice will be recruited. The sampling of nursing staff follows a qualitative approach and aims to ensure the representativeness of the target group [38] by contrasting characteristics such as gender and professional experience.

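### The staff drop-out rule removes nurses on grounds related to the staff outcomes, so reported acceptance and technology affinity may be overstated

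*Protocol article*

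**What the plan says.** Two removal rules stand under Dropout criteria of the secondary target group in the protocol article.

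- The first is discretionary: "nursing staff can be excluded from the study if their poor technical affinity or acceptance leads to massive restrictions" in using the system correctly.
- The second is worded as mandatory and applies in the one-to-two-week test phase. If "a professional is found to lack technical user skills or feedback is received from the person concerned", then "this person will not continue to participate in the study".

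The Exclusion criteria of the secondary target group give only two grounds for exclusion: no written consent, or no responsibility for the residents' incontinence care.

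The section on endpoints of the secondary target group plans "interviews regarding the acceptance, experience and perceived effects of the digital assistance systems" and the resulting changes in work processes. Staff are also to be "surveyed quantitatively about their subjective attitude toward the use of technology in their professional context", using a shortened and adapted TA-EG. Table 2 schedules both the acceptance interview and the modified TA-EG at t0, t1, t2 and t3. The staff strand is described under Methods and design as single-armed and observational, with every participant surveyed both quantitatively and qualitatively at all four time points.

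On numbers, the abstract gives 15–20 nursing staff who "will be interviewed regarding the effects, experience, acceptance and satisfaction". The Power calculation section recruits "about six to eight individuals in each inpatient facility", and there are four facilities.

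**The concern.** A nurse who does not accept the system, or cannot work with it, is an observation on the staff outcomes. If such nurses leave the study and nothing further is collected from them, the remaining sample leans towards those who manage and like the system. With a single arm, this selection cannot cancel against a comparator.

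The Background says that scepticism among nursing staff is frequent with such systems. The section on inclusion of staff wants the sample to reflect heterogeneity. The Objectives ask how the technology can be built into routine care, and the Discussion promises recommendations on transfer to standard care. Staff who could not or would not use the system are among the most informative for those questions.

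**Working it through.** **Rules against outcomes.**

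- The discretionary rule names affinity and acceptance as the reason for removal. Affinity is what the TA-EG is built to measure, and acceptance is an interview outcome.
- The mandatory rule names user skills or feedback. These are not the outcomes themselves but can plausibly correlate with them.
- The article describes no further interview, questionnaire or count for removed staff.

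**Size.** The article states no figure for staff acceptance or staff removal, so there is none to reproduce. An illustration needs two assumptions: the fraction removed, f, and the correlation, r, between the removal ground and the outcome score. Take the removal ground as standard normal, remove the lowest fraction f, and let the outcome depend linearly on it. The mean of those who remain then exceeds the mean of all staff by

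shift = r × φ(z_f) / (1 − f), in SD units,

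where z_f is the f-quantile and φ the density of the standard normal.

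| f (assumed) | z_f | r = 1 | r = 0.3 |
|---|---|---|---|
| 5% | −1.645 | 0.103/0.95 = 0.109 | 0.033 |
| 10% | −1.282 | 0.175/0.90 = 0.195 | 0.058 |
| 20% | −0.842 | 0.280/0.80 = 0.350 | 0.105 |
| 30% | −0.524 | 0.348/0.70 = 0.497 | 0.149 |

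The range is about 0.03 to 0.50 SD. With f = 0 or r = 0 the shift is zero; for any positive r it is upward. The calculation applies directly only to a score such as the modified TA-EG. For the interviews the same selection appears as under-represented critical accounts, which has no SD.

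**Order of t0 and removal.** The article can be read two ways.

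- The drop-out section places training at the beginning of the measurement period, with the test phase after it. A t0 value may then exist for staff who are later removed.
- The Interventions section places training and testing before the realisation phase, which it calls the actual trial. The Measurement period section puts t0 at the start of the four months. Staff removed in testing would then have no t0 value.

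On the first reading, comparing the TA-EG mean at t0 with that at t3 mixes change within persons with the loss of low scorers. On the second, test-phase removals cannot distort the trend, but the sample is selected before measurement starts. Later discretionary exclusions could still affect the trend on either reading.

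**Staff number, a separate matter.** Four facilities × 6 = 24 and 4 × 8 = 32, against 15–20 in the abstract. Treating the 15–20 as an interviewed subset does not fit the statement that all staff participants are surveyed qualitatively.

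**The case against.** The first rule is narrower than it may look. It is optional and applies only when poor affinity or acceptance seriously hampers correct use, so a sceptical nurse who operates the system adequately stays in. The mandatory rule turns on skills or feedback, not on acceptance. The rules have a legitimate stated purpose, to secure correct application of the technology. The section on possible harms expects some participating staff to feel burdened or overloaded and plans to talk with them. All of this stands. A reader might infer that every nurse with low acceptance is removed and that the study can describe only those who already accept the system; the text does not support that.

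A reader might also infer that mean acceptance will rise artificially from t0 to t3. Acceptance is collected by interview and examined by qualitative content analysis, and the article describes no acceptance scale or mean. Only the TA-EG could show such a rise, and only if removal comes after t0, which the article leaves open.

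A single figure for the bias would be unsupported too, because it would need a number removed that the document does not give and a removal ground that tracks the outcome perfectly.

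The full protocol, which is not shown, may provide for exit interviews or for reporting of excluded staff. That is possible, but the point concerns a rule the article does state, namely that these persons do not continue. An analysis plan cannot recover data that were never collected. It is also fair to say that exclusion criteria may be meant for entry and drop-out criteria for later. The two lists still need to be made compatible, because the first is worded as exhaustive.

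**Conclusion.** The point holds as a risk of selection related to the outcome. Reported staff acceptance and affinity may be overstated, provided the removal grounds correlate positively with those outcomes. The size is unknown: 0.03–0.50 SD is an illustration under an assumed 5–30% removed, an assumed correlation of 0.3–1 and a normal scale. Whether the consequence is a distorted TA-EG trend or only an unrepresentative sample depends on the order of t0 and the test phase.

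The affected outcomes are secondary and belong to the staff strand. Nothing here shows a bias in the residents' comparison of falls. The conflict over the number of staff is real, but it is a separate inconsistency and no evidence of selection.

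**What to change.** - Limit the drop-out rule to operating the system. Staff who meet it may stop using the system but, unless they withdraw consent, remain in the staff sample.
- Have them complete the remaining questionnaires and interviews, or at least one exit interview and one modified TA-EG.
- Report how many were removed from use, and why, as an acceptance result. Give the staff results both for all trained staff and for those who continued.
- State whether t0 comes before or after the test phase.
- Reconcile the exclusion list for staff with the drop-out rules.
- Separately, give one staff number in the abstract and the Power calculation section. If only 15–20 of 24–32 are to be interviewed, say so and amend the statement that all are surveyed qualitatively.

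The cost is wording plus a few short extra contacts by study staff who already visit the facilities.

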### Interventions

The RCT addresses the use of digital assistance technologies in the field of incontinence care for care recipients. The RCT plans to equip incontinence products of any type (urine and stool) with a sensor that transmits care-related information to connected systems (such as smartphones and PCs). A local tracking mechanism allows the incontinence product to be located, but this function will not be used within this RCT.

The sensor technology can be used within the facilities even without a dedicated W-LAN, as it is used via a Bluetooth Low Energy (BLE) as well as via LTE network; set up by AssistMe GmbH (practice partner). AssistMe provides the complete sensor, hardware and network technology. This also includes the smartphones provided to the nursing staff.

At this stage multiple utilization of the sensors with incontinence material is not possible for the entire course of this study. However, in some cases, particularly at the start of the RCT, sensors will undergo a re-use process (including cleaning, disinfection, etc.) to check and test if and to what extent multiple utilization is possible. In view of the above, a multiple utilization of the sensors will be aimed at for test purposes, in order to identify opportunities for cost-effective mass production while also ensuring a sustainable use of the product. The project in applied practice thus enables further investigations which can provide recommendations for mass production of incontinence products equipped with (printed) sensors. The experience of the practical partner AssistMe GmbH in the field of cleaning and disinfecting sensor technology will also be used for quality assurance and development of logistical recommendations.

The digital assistance system from AssistMe GmbH provides the responsible nursing staff within the care facilities with an automated message concerning the status of the incontinence material (ICM) of the home residents within the IG. The status report does not give any indication about whether the ICM needs to be changed but only describes the status of the ICM itself (for example, 1st urination, 2nd urination, 3rd urination). The decision to change the ICM is made by the responsible nursing staff and not by the digital assistance system from AssistMe GmbH. In addition, it is possible to store individual incontinence profiles of the home residents in order to obtain an additional source of information concerning the decision among the nursing staff as to when an optimal change of the ICM should take place.

The digital assistance system from AssistMe GmbH is to be understood as a supporting, digital measure in the context of incontinence management.

The technical procedure of the intervention is divided into three phases:Preparation and implementation phaseTraining and testing phaseRealisation phase

(1) Preparation and implementation phase

This thus implies, on the one hand, the implementation of an IT infrastructure within the care facility and the associated assurance of a complete connectivity of the wearables (explanation, follows below) equipped to the ICM with the network. On the other hand, the logistical process of the ICM requirements for the home residents will be jointly coordinated in detail with the respective care facilities and service providers (TZMO and geria + med) so that a) no supply bottlenecks arise and b) the study process can be realized as smoothly as possible.

(2) Training and testing phase

The training and testing phase is used to familiarise the participating nursing staff with the digital assistance system from AssistMe GmbH. This means both a multi-hour training session for nursing staff and a 1–2 week trial period to "get to know" and "better understand" the system will be conducted, in order to reduce any technical challenges during the course of the study and to address any questions that arise from the nursing staff in advance.

(3) Realisation phase

The realisation phase represents the actual RCT and intervention. In this phase the digital assistance system is connected within the nursing facility, the nursing staff has been trained and the study project begins (see Fig. 2).

**Fig. 2 Fig2:**
[figure not shown]
Overview of the digital assistance system from AssistMe GmbH

The ICM equipped with a sensor is worn with a so called wearable. The wearable records the sensor data and transmits the data via BLE to the corresponding charger or repeater nodes.

The charger and repeater nodes act as network within the nursing facility ensuring a permanent connectivity between wearable and IT infrastructure. The charger and repeater nodes record the signal transmitted via BLE and then forward it via WLAN to defined access points within the nursing facility. These access points send the relevant data to an edge computer in the corresponding nursing facility and then to a LTE router which sends the data to the AWS cloud service, which complies with data protection requirements. The data is processed in the cloud and then forwarded to the mobile application of the responsible nursing staff.

Two wearables will be individually assigned to each resident of the IG and will be accordingly available to the nursing staff. Hence one wearable can be worn with the ICM while the other wearable is charging on the station (charger node) ensuring a seamless change of the wearable when the battery is low.

The aim is to implement a fully functioning end-to-end system in the nursing facility so that the ICM status of each facility resident can be monitored in real time on the smartphone of the responsible nursing staff.

### Endpoints

#### Endpoints of the primary target group (care recipients with urinary and faecal incontinence)

Occurring falls represent the primary endpoint of the RCT. Secondary endpoints include cognitive ability, quality of life, sleep quality and disruptions of sleep, incontinence material consumption and general health.

#### Endpoints of the secondary target group (nursing staff)

The secondary target group will be surveyed by means of interviews regarding the acceptance, experience and perceived effects of the digital assistance systems and the resulting changes to their work processes (secondary endpoints). This qualitative data collection captures the important perspectives of nursing staff and nursing management.

In addition, the nursing staff will also be surveyed quantitatively about their subjective attitude toward the use of technology in their professional context and concnerning the use of the digital assistance system in particular. The subscales of the questionnaire to measure the affinity for technology scale (TA-EG) are used as guidance. The TA-EG consists of 19 items and four scales and has been adequately reviewed in terms of its validity and reliability. Due to its scope, it will be used in a shortened form in the study and adapted to the specific core of the intervention. The modified questionnaire was tested in pretests with regard to comprehensibility, practicability and temporal scope. Subsequently, editorial changes were incorporated (see Table 1).

**Table 1 Tab1:** Endpoints and measurement tools for the primary target group

Primary endpoints	Measurement tools
Incipient falls	**STRATIFY instrument** (St. Thomas’s risk assessment tool in falling elderly inpatients) [39] • Includes five items / risk factors • Confirmed validity and reliability [40] • Quantitative method, third-party assessment **Tinetti Test** [41] • Includes 17 items • Confirmed validity and reliability [42] • Quantitative method, third-party assessment **Extrinsic and intrinsic risk factors** for the residents • based on and correlating with the national expert standard on incontinence of the German Network for quality standards in care-giving (DNQP) [11] **Analysis of fall records** • Documentation through the nursing facility is mandatory • Provides important information about occurring falls and possible consequences of falls
**Secondary endpoints**	**Measurement tools**
Cognitive ability	**Mini Mental Status Examination (MMSE)** [36] • Consists of five categories with a total of 11 items • Confirmed validity and reliability • Used for stratification • Quantitative method, self-reported scale
Quality of life	**Quality of life in elders with multimorbidity (FLQM**) [43] • Consists of three items • Confirmed validity and reliability • Qualitative and quantitative method, self-reported or third-party assessment scale
Sleep quality and disruptions of sleep	**Karolinska Sleepiness Scale (KSS)** developed by [44], German version based on [45] • Includes 1 item • Not yet validated for older people or geriatric patients • Quantitative method, self-reported or third-party assessment **Richard Campbells Sleep Questionnaire (RCSQ)** • Consists of 5 items • Quantitative method, self-reported or third-party assessment
Consumption of incontinence materials	**Complete documentation** of material usage
General health	Analysis of the nursing documentation for incipient chronic diseases & changes in the severity of existing diseases

